### Policy landscape analysis

The aim of the policy landscape analysis is to identify opportunities for strengthening implementation of food policies to reduce NCDs in Fiji and Samoa. The primary question we will be addressing through the prospective policy analysis is: *What are the potential opportunities and challenges to strengthen policies for prevention of diet-related NCDs in Samoa and Fiji?* Because of their focus on policy change, Walt and Gilson’s health policy analysis triangle [34] and Kingdon’s theory of agenda setting and policy change [35] will inform the study design and development of instruments for data collection. The data collection will focus on 1) the existing policy content, 2) relevant stakeholder actions and perspectives, 3) industry corporate political activity, and 4) the political economy relevant to food and nutrition, informed by previous approaches to policy landscape analysis [36].

#### Documentary analysis

We will conduct a desk-based review of policy content for Fiji and Samoa relevant to diet-related NCD prevention. Policy documents will be identified, based on searches of government websites and direct approaches to government ministries with responsibilities related to food and/or nutrition. Policies in scope will include whole-of-government policy statements, such as the National Development Plan; sectoral policy documents, such as the National Nutrition Policy, and implementation-focussed documents. Relevant content from each of these policies will be extracted to a predetermined matrix based on the study frameworks [36]. This will include information regarding: policy objectives and activities (with reference to the Food Policy Options agreed in the WHO Global Plan of Action for the Prevention and Control of NCDs 2013–2020 [37]); framing of policy problems and solutions (including any mention of gender disparities, institutional responsibilities, co-ordination and implementation mechanisms, and resourcing).

We will draw on this policy content analysis to then conduct a stakeholder analysis to identify the influential actors relevant to diet-related NCD prevention policy, including industry, government and non-government stakeholders [36]. Stakeholders will be defined as: “actors who have an interest in the issue under consideration, who are affected by the issue or who – because of their position – have or could have an active, or passive, influence on decision making and implementation. They can include individuals, organizations, different individuals within an organization, and networks of individuals and/or organizations, i.e. alliance groups” [38]. We will identify such stakeholders and their interests and influence in Fiji and Samoa through 1) searching websites of relevant Government sectors, organizations, institutions and industry actors operating in the country, 2) searches of academic literature, 3) the policy content analysis, and 4) key informant interviews (see details below). We will use a matrix to document the following attributes of identified stakeholders: interest relevant to food and nutrition as a policy issue; level of interest; perceived level of influence/power; source of power/influence; outcomes including impacts on policy [38].

The stakeholder analysis was complemented by an analysis of corporate political activity of the food industry in Fiji and Samoa, based on methods developed by Mialon and colleagues [39]. This will update the analysis already undertaken in Fiji [40]. Data will be collected through searches of industry websites, online media websites and industry analytical reports (e.g. Euromonitor). For each industry actor identified, we will document available information on: Information and messaging; Financial incentives; Constituency building; Legal; Policy substitution; Opposition, fragmentation and destabilization.

#### Key-informant interviews

We will conduct semi-structured interviews with approximately 15–20 key informants in each country, designed to understand the policy and political context, implementation issues, as well as identify facilitators and barriers to implementing different policies. Potential interviewees will be identified based on the desk-based policy content and stakeholder analysis, as well as direct requests to government ministries and other actors relevant to food and/or nutrition policy. The semi-structured interview schedule will be based on the policy theory underpinning the study and will be piloted with two relevant experts who won’t be involved in the final interviews. Interviews will be recorded, where permission is granted, and transcribed in full.

#### Policy analysis

Our analysis will focus on identifying potential policy gaps and opportunities, as well as contextual and politico-economic considerations that might inhibit or foster policy change. The data will be analysed iteratively throughout the data collection process, to identify additional interviewees and potential opportunities to follow up on. We will use NVivo for data management and coding. The data from the policy content, stakeholder and corporate political activity analysis will first be analysed separately, to identify policy strengths and gaps, influential stakeholders, and industry interests and influence. The qualitative data from the interviews will be coded using pre-determined themes based on the study frameworks and then data from all sources will be analysed thematically to 1) understand opportunities for policy change to support improved food systems and nutrition for the prevention of diet-related NCDs, and 2) understand the political economy of food policy in the study countries drawing on Campbell’s approach to political economy analysis [41], which highlights the influence of ideas and understandings of the policy problem and policy solutions, as well as the existing policy and political context (including how long the policy has been in place and when it was evaluated) in shaping opportunities for policy change.

### Repeat cross-sectional surveys to understand dietary intake and behaviours and composition and prices of foods

#### Collating existing relevant data

For each country, we will access and analyse relevant data from existing recent surveys as well as undertake new surveys to inform intervention implementation and monitoring building on the investigators’ recent systematic review [42]. Existing surveys will include the most recent Food and Agriculture Organization (FAO) Household Income and Expenditure Surveys (HIES) [43], WHO Stepwise Approach to Assessment of NCD Risk Factors and (STEPS) [24] and National Food and Nutrition Surveys (NFNS) [44] and any relevant research studies that have looked at diet or food composition. Both Fiji (2010, 2016) [45] and Samoa (2011, 2017) [46] have participated in the Global School Based Student Health Survey, which includes information on body mass index and frequency of soft drink consumption from 12 to 17 year olds. Relevant existing data will be extracted from all recent surveys and tabulated with dates of data collection.

#### 24-h diet surveys

The objective of the 24-h diet recall surveys is to provide an in-depth robust assessment of what adults are eating, including the contributions of different foods to salt and sugar in the diet. 24 h diet recall surveys can be used to accurately assess changes in population intake of nutrients [47]. Urinary analysis is the best way of estimating sodium intake. However, both Fiji and Samoa monitored sodium intake using urinary analysis in 2013 and 2016 [48, 49] and it is not expected to have changed since then. Additionally, spot urine samples will be collected as part of the next WHO STEPS surveys in each country (planned for 2021), so it is not necessary to include urinary sodium analyses as part of this project. In contrast, whilst Fiji has a National Diet and Nutrition Survey (NDNS) from 2015, this will not be repeated until 2025. We will, therefore, undertake dietary surveys in years 1 and 4 in Fiji and 2 and 5 in Samoa.

##### Sampling

Surveys will be undertaken in 3600 adults in Fiji (Viti Levu) in year 1 and 4, and in Samoa (Upolu) in years 2 and 5. We have selected the main islands based on prohibitive cost and time associated with travelling to the outer islands. The samples will be stratified into equal numbers of men and women in two age groups (18–44 and 45–69 years). The sampling strategy will be based on the recent National Nutrition survey (NNS) in Fiji and the most recent WHO STEPS project in Samoa [50]. Each used a two-stage sampling process, based on census information, to obtain representative samples for selected regions. Sampling in Fiji will also be stratified by the two main ethnic groups (Indigenous Fijians, and Indo Fijians). The age, sex and region of randomly selected individuals that do not wish to participate will be recorded, such that response rates and the likely impact of non-response can be estimated.

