##### Sample size and power for evaluating impact of food policies

To determine the sample size for salt, we have used the standard deviation from recent surveys in Fiji and Samoa (SD: 3.6) which used urine collection [51], with the knowledge that the standard deviation is likely to be lower using a dietary questionnaire [52], which would mean our sample size calculation will be conservative We have estimated the standard deviation of the proportion of dietary energy from free sugar (SD: 5.4) from a recent large survey (the 2011 Australian Health Survey). With a design effect of 1.5 to account for clustering and stratification, we will need 300 participants in each country at each time-point to reach 0.9 power with a t-test to detect a 1.2 g reduction in salt consumption. For free sugar we estimated that we have 0.9 power to detect a change of 1.8% absolute decrease in the proportion of dietary energy from free sugar between time points. A response rate of about 50% is anticipated, based on our previous work in these settings [53], so 600 individuals will be approached in each country.

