### Local training and research capacity building

Because of the growing burden of diet related disease and the related need for expertise in this area, increasing food policy research capacity in both Australia and the Pacific Islands will be an underpinning objective of this project. We will do this based on the principles of the Collective Action Framework which emphasizes “the importance of having a common agenda, common progress measures, mutually reinforcing activities, continuous communication, a backbone organization with staff and a specific set of skills” [60]. The investigator team comprises of senior academics who will provide mentoring and support to the early career researchers in the different countries. The objective will be to increase research capacity at all levels in Australia and the Pacific with a view to translating this experience globally. Effective food policy is needed in Australia as much as it is in Fiji or Samoa and we believe expertise gained through this research can and should be applied in all countries. All phases of the project will be implemented in Fiji and Samoa by a local researcher supported by the Head of the Pacific Research Centre for the Prevention of Obesity and NCDs based at Fiji National University (FNU) in Fiji. In addition, 3–4 research assistants will be recruited during the 4 months required to undertake the surveys during baseline and follow-up assessment. A 5-day program of training in dietary assessment and STICKE will be carried out prior to the initial baseline assessment. Further on-going training and support will be provided during the intervention stage.

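### The Sampling section puts the diet survey at 3600 adults, but the sample size section puts it at 300 participants (600 approached) per country and time-point, and the two cannot be reconciled

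*Protocol article*

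**What the plan says.** Two adjacent sections under 24-h diet surveys give the size of the same surveys.

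- **Sampling:** "Surveys will be undertaken in 3600 adults in Fiji (Viti Levu) in year 1 and 4". This sentence then extends the plan to Samoa, one year later in each round. It does not say whether 3600 is per country, per round or overall, or whether it counts people approached or people surveyed. Its plain sense is people surveyed.
- **Sample size and power for evaluating impact of food policies:** "we will need 300 participants in each country at each time-point to reach 0.9 power with a t-test", for a salt reduction of 1.2 g. Then "A response rate of about 50% is anticipated, based on our previous work in these settings", and from that, "so 600 individuals will be approached in each country".

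The second section also gives the inputs: an SD of 3.6 for salt, an SD of 5.4 for the percentage of dietary energy from free sugar, a design effect of 1.5, and a free-sugar target of 1.8 percentage points at 0.9 power. It states neither the significance level nor whether the test is one- or two-sided. No sentence anywhere in the article connects 3600 with 300 or 600.

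**The concern.** Survey procedures makes these surveys the source of the primary outcomes: mean sodium and sugar intake by gender, and their change over the study. Results are also promised by sex, age and, in Fiji, ethnicity. A reader who wants to know how precise those results will be meets two sizes that differ 12-fold (3600/300). With the equal split by sex that Sampling describes, 300 gives 150 men and 150 women per round, and 3600 would give 1800 of each. The size of the main survey, and so the smallest change it can detect, cannot be read from the article with confidence.

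**Working it through.** **Inputs.** All are from the sample size section: salt SD 3.6 (taken as g per day), difference 1.2 g, sugar SD 5.4 and difference 1.8 points, design effect 1.5, power 0.9, response about 50%. The comparison is between two independent cross-sections of equal size within a country. Assumption: two-sided 5%, so z = 1.960 + 1.2816 = 3.2415.

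**1. Reproduce the article's 300.**
- Per round before the design effect: n = 2 × (3.2415 × SD/difference)² = 2 × (3.2415 × 3.6/1.2)² = 189.1, rounded up to 190.
- Times the design effect: 190 × 1.5 = 285. With the t distribution, 190.1 rounds up to 191, and 191 × 1.5 = 286.5, so 287.
- Power at 300: the effective size is 300/1.5 = 200 per round. SE = 3.6 × √(2/200) = 0.36. 1.2/0.36 − 1.960 = 1.373, giving power 0.915 (0.914 with the t distribution).
- Sugar has the same standardised difference (1.8/5.4 = 1.2/3.6 = 1/3), so it gives the same n and power.
- Sensitivity to the assumption: one-sided 5% needs 155 × 1.5 = 232.5, so 233, and gives power 0.954 at 300. That fits the stated 300 and 0.9 less well.
- Number approached: 300/0.5 = 600, exactly as stated.

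The section is therefore coherent, with 300 a modest round-up.

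**2. Look for a route to 3600.**

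| Reading | Total |
|---|---|
| Completed, 2 countries × 2 rounds | 300 × 4 = 1200 |
| Approached, 2 countries × 2 rounds | 600 × 4 = 2400 |
| Approached if 3600 are completed per country and round | 3600/0.5 = 7200 |
| Completed if 3600 are approached | 3600 × 0.5 = 1800 |
| 3600 spread over 2 countries × 2 rounds | 3600/4 = 900 |

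None of these links 3600 to the stated 300 or 600.

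**3. What the difference amounts to.** The change detectable at 0.9 power is 3.2415 × SD × √(2 × 1.5/n). The 95% half-width for one mean is 1.96 × SD × √(1.5/n).

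| Completed per country and round | Power for 1.2 g | Detectable salt change | Detectable sugar change | Half-width, mean salt |
|---|---|---|---|---|
| 300 | 0.915 | 1.17 g | 1.75 points | 0.50 g |
| 3600 | above 0.999 | 0.34 g | 0.51 points | 0.14 g |

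The ratio of detectable changes is √12 = 3.46.

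**The case against.** The best defence is that 300 is a minimum for the stated target and that a larger survey was planned, perhaps to serve the sex, age and ethnicity comparisons. The article does not say so, and the defence fails on the number approached: 600 invitations cannot produce 3600 surveys. Nor is this a detail that an article may leave to a fuller document, since both figures are printed in running prose.

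Three stronger readings are tempting, and the article does not support them.

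- **Power is at risk.** It is not, for the stated target. Both conflicting sizes exceed 0.9 power for 1.2 g. What is contradictory is the size. The article gives no power or precision figure for 3600 that could conflict with the one for 300.
- **600 covers both rounds.** The sentence on the number approached leaves out the time-point, so a reader might infer 300 approached and 150 completed per round, with power of about 0.65. But the sentence derives 600 from the per-time-point 300 and the 50% response, so it is a per-time-point number. The missing words are a drafting gap.
- **3600 is impossible to field.** Local training and research capacity building says "3–4 research assistants will be recruited during the 4 months required to undertake the surveys during baseline and follow-up assessment". A reader might infer that this rules 3600 out. However, the article gives neither field days nor interview length, and does not say clearly whether the staffing is per country. Any daily workload would rest on assumed figures, and the conflict stands without it.

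One part of the defence stands: only the authors know what was meant. The arithmetic marks 3600 as the outlier, but does not show whether the sentence was meant to give completed or approached numbers.

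**Conclusion.** The contradiction is real, and the Sampling figure cannot stand beside the sample size section as written. The 300 completed and 600 approached per country and time-point agree with each other and with the stated inputs. The 3600 follows from nothing in the article and is probably an error. The consequence is an unclear survey size and roughly a 3.5-fold uncertainty in the detectable change (1.17 g against 0.34 g of salt). The sample size calculation itself is sound. These figures rest on the article's SDs and design effect and on an assumed two-sided 5% level. A one-sided level would change the numbers but not the conclusion.

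**What to change.** The authors should first confirm the intended size, then state one figure in both sections, labelled as completed or approached, per country and per time-point.

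- If the sample size section is right, as its arithmetic suggests, the Sampling sentence should give 300 adults (about 600 approached) in each country at each time-point in place of 3600. As a clarification, the time-point should also be added to the sentence on the 600 approached.
- If 3600 is intended, the power statement, the detectable differences (about 0.34 g salt and 0.51 points sugar if 3600 is completed per country and round) and the number approached (about 7200 per country and round at 50% response) must be restated to match.

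Stating the significance level and sidedness in the same edit would let readers reproduce the figure. The first case costs a wording change in two sentences. The second also requires the sample size section to be rewritten.

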##### Sample size and power for evaluating impact of food policies

To determine the sample size for salt, we have used the standard deviation from recent surveys in Fiji and Samoa (SD: 3.6) which used urine collection [51], with the knowledge that the standard deviation is likely to be lower using a dietary questionnaire [52], which would mean our sample size calculation will be conservative We have estimated the standard deviation of the proportion of dietary energy from free sugar (SD: 5.4) from a recent large survey (the 2011 Australian Health Survey). With a design effect of 1.5 to account for clustering and stratification, we will need 300 participants in each country at each time-point to reach 0.9 power with a t-test to detect a 1.2 g reduction in salt consumption. For free sugar we estimated that we have 0.9 power to detect a change of 1.8% absolute decrease in the proportion of dietary energy from free sugar between time points. A response rate of about 50% is anticipated, based on our previous work in these settings [53], so 600 individuals will be approached in each country.

##### Recruitment process

For the general population, in line with local customs, individuals will be informed about the study and invited to participate through a face-to-face invitation made by an interviewer visiting the household. Prior to this, contact will be made with the local village chief to request permission to enter the village and carry out the work. Activities to raise community awareness will also be undertaken. If no one suitable is available in the household when the interviewer calls, a repeat visit will be made, or interviewers will attempt to locate the head of the household by visiting local community centres and other meeting places.

##### Data collection process

Research assistants will be trained in the 24-h diet recall survey data collection procedures. The entire enrolment and data collection process will be done face-to-face in English (which is spoken by more than 90% of the populations in these countries) by trained research assistants. Research assistants will be able to assist participants by orally translating written material into the local language. Participant information sheets and consent forms will be available in Hindi and Fijian (for Fiji). Each consented participant will then be assigned a unique ID number. Participants will then be interviewed by the research assistant to:i.Complete a general questionnaire on basic demographics, disease history and medication useii.Complete the 24-h diet recall survey (see below for more details)iii.Record height, weight, waist circumference and blood pressure [53]

##### Survey procedures

The dietary survey will be a 24 h recall using the multiple pass method [54]. Trained research assistants will use supportive visual tools showing portion sizes for locally-appropriate foods to improve accuracy. Pilot testing of this approach will be undertaken by the research assistants. Discretionary salt intake will also be estimated using previously tested methods [55]. The dietary survey data will be entered into FoodWorks nutrition analysis software [56] using established standard procedures. The FoodWorks program has already been adapted to contain Pacific Island food composition data. The parallel food composition (FoodSwitch [57]) surveys in the two sites (see 2.3 below) will provide more up to date nutrient content data processed foods and these will be incorporated into the FoodWorks dataset. The FoodWorks software enables both an overall estimate of salt and sugar intake as well as the main sources of salt and sugar in the diet.

The *primary outcomes* for the dietary surveys will be gender-disaggregated average levels of sodium and sugar intake levels for adults, and any changes during the study. Key secondary outcomes will be the main sources of sodium and sugar in the diet. Population estimates will be obtained by weighting according to the sample design and the age/gender population structure based on Census data. The results will also be reported for major participant subgroups defined by sex, age and ethnicity (Fiji only) and evidence for differences between subgroups examined using t-tests.

*Reporting results to participants* - The summary results of the 24-h diet recall survey will be distributed to all participants who expressed interest in receiving the results by either email or postal address as part of the consent process. The information provided will include estimated population daily sodium and sugar intakes and how this compares to current national guidelines for salt and sugar. This will be accompanied by simple advice about how to eat a healthy diet low in salt and sugar and high in fruit and vegetables. Phone and email support will be available for 12 months after the last of the baseline and follow-up results letters have been dispatched.

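### The dietary surveys' primary outcomes are defined by gender, but the stated 0.9 power holds only for men and women pooled; on the same inputs it is about 0.65 within each sex

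*Protocol article*

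**What the plan says.** Three places in the protocol article's account of the 24-h diet surveys bear on this.

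- **Survey procedures** defines the primary outcomes: they "will be gender-disaggregated average levels of sodium and sugar intake levels for adults, and any changes during the study".
- **Sample size and power** fixes the number for salt: "we will need 300 participants in each country at each time-point to reach 0.9 power with a t-test to detect a 1.2 g reduction". It claims the same power for a fall of 1.8 percentage points in the share of energy from free sugar. The inputs are SDs of 3.6 (salt) and 5.4 (sugar) and a design effect of 1.5. Analysis by sex is not mentioned. At an expected response of about 50%, 600 people are to be approached in each country.
- **Sampling** sets the split: "The samples will be stratified into equal numbers of men and women in two age groups (18–44 and 45–69 years"). The same section gives the survey size as 3600 adults.

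The opening part of the Methods also lists changes in population intake of salt and sugar among the main outcomes, without reference to gender.

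**The concern.** The outcome called primary is a set of sex-specific quantities, while the sample size appears to be worked out for one comparison of all adults between two waves. If so, the 0.9 belongs to a contrast that the definition does not name, and the contrast that it does name has only half the sample. A reader would credit the sex-specific changes with a precision that the design does not give them. A non-significant change in men or in women would then look more informative than it is.

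**Working it through.** **Inputs.** From the sample size section: 300 per country per wave, design effect 1.5, salt change 1.2 g with SD 3.6, sugar change 1.8 points with SD 5.4. From the Sampling section: equal numbers of men and women, so 150 of each. Assumed, because the article does not state them: two-sided alpha 0.05, and the same SD, target change and design effect within each sex as overall. Normal approximation unless noted; the multiplier for 0.9 power is 1.960 + 1.2816 = 3.2415.

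**Step 1: reproduce the stated figure.** Both targets are one third of an SD (1.2/3.6 = 1.8/5.4 = 1/3), so salt and sugar give the same answers.

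- Required n per wave under simple random sampling: 2 × (3.2415 × 3)² = 189.1. Times 1.5 = 283.7, so 284. The t-test version gives 191 × 1.5 = 286.5, so 287. Either is consistent with a rounded 300.
- Power with all 300: effective n = 300/1.5 = 200; SE for salt = 3.6 × √(2/200) = 0.36; 1.2/0.36 = 3.333; power = Φ(3.333 − 1.960) = 0.915 (0.914 by the t-test).
- One-sided 0.05 would need only 231 and would give 0.954 with 300, so it does not explain the plan's number. That is the reason for assuming two-sided 0.05.

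The stated power is therefore that of the pooled comparison.

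**Step 2: the same calculation within one sex.** Effective n = 150/1.5 = 100 per wave.

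| | Salt | Free sugar |
|---|---|---|
| SE of the change | 3.6 × √(2/100) = 0.509 g | 5.4 × √(2/100) = 0.764 points |
| Target/SE | 1.2/0.509 = 2.357 | 1.8/0.764 = 2.357 |
| Power | 0.654 (t-test 0.650) | 0.654 (t-test 0.650) |
| Detectable at 0.9 power | 3.2415 × 0.509 = 1.65 g | 3.2415 × 0.764 = 2.48 points |

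**Step 3: sensitivity to the assumptions.**

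- *Smaller salt SD* (150 per sex, design effect 1.5): power 0.73 at SD 3.3, 0.81 at 3.0 and 0.92 at 2.5. Power of 0.9 needs an SD of about 1.2/(3.2415 × √0.02) = 2.6. For sugar the matching value is 1.8/(3.2415 × √0.02) = 3.9, against the stated 5.4.
- *Smaller design effect within sex*: an illustrative 1.25 gives effective n = 120 and power 0.73 at the stated SDs, or 0.87 for salt with SD 3.0.
- *One-sided 0.05*: 0.76.
- *Survey size*: if 3600 were the number per wave, or the total over two waves in one country, by-sex power would exceed 0.99. If it were the total over both countries and both waves (900 per country per wave, 450 per sex, effective 300), it would be about 0.98.

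**Step 4: size needed for 0.9 within each sex at the stated targets.** 284 to 287 per sex, so 568 to 574 per wave in each country, and at 50% response 1,136 to 1,148 approached.

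**The case against.** The best reply is that the pooled change was always the intended contrast. The main outcomes refer to population intake, and the power statement is per country. The paragraph that defines the primary outcomes goes on to promise population estimates weighted to the age and gender structure, and then says that results will also be reported by sex. No test between waves within each sex is specified. On that reading, gender disaggregation is a reporting format. This is plausible and it stands, but it does not remove the mismatch. The definition as printed is by gender, and sex then appears again as a subgroup. If the pooled change was meant, the definition should say so.

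A second reply is that 0.65 is not a firm number. This also stands in part. The authors chose the salt SD "with the knowledge that the standard deviation is likely to be lower using a dietary questionnaire", so by-sex power for salt may be higher. If men and women come from the same clusters, the clustering part of the design effect may shrink within sex. Alpha is not stated. But no lower SD is given for salt, the remark does not extend to sugar, and neither a design effect of 1.25 nor a one-sided test brings sugar to 0.9.

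A reader might go further and infer that non-significant sex-specific results are likely even if the target is met, or that the survey has only about a 0.43 chance of success (0.654 squared, both sexes significant on one nutrient, if independent). The article does not support either. At power 0.65 the chance of a non-significant result in a given sex is 0.35, which is substantial but less than even, and no rule requires both sexes to reach significance. Nor does impact rest on one test: the evaluation draws on several outcomes and a process evaluation.

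**Conclusion.** The point holds in a conditional form. The 0.9 power attaches to the all-adult change between waves, not to the gender-disaggregated change that is named as primary. By-sex power is about 0.65 for both nutrients, and the by-sex changes detectable at 0.9 power are about 38% larger than the targets (1.65/1.2 and 2.48/1.8). These figures rest on 300 participants per country per wave, an equal sex split, two-sided alpha 0.05, the stated SDs and a design effect of 1.5 carried over within sex.

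It would be too strong to say without condition that the design has 0.65 power by sex. The 3600 adults in the Sampling section would reverse that conclusion. The power statement is tied explicitly to 300 participants from 600 approached, so 300 is the better-supported basis, but the two sections contradict each other and the by-sex figure cannot be final until they are reconciled.

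**What to change.** In the Survey procedures section, name the weighted all-adult change between waves in each country as the primary contrast for salt and for free sugar. This agrees with the main outcomes and with the sample size calculation. List the sex-specific changes as key secondary estimates with confidence intervals.

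If the gender-disaggregated change is to stay primary, add to the sample size section that power within each sex is about 0.65 for 1.2 g and 1.8 points, and that about 1.65 g and 2.5 points are detectable at 0.9.

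In either case, state alpha and sidedness, and reconcile the 3600 with the 300 participants and 600 approached. If the larger number is the true one, the power statement has to be recalculated.

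The cost is wording only, with the same data and sample. The downside is that sex-specific results either lose primary status or carry a less favourable stated power. Keeping both the by-sex primary and 0.9 power would instead mean nearly doubling the 300 per wave.
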